### Design

Individuals in the UIA follow-up cohort will be allocated to two groups, a modeling and a validation group, in a ratio of 2:1. Taking the annual rupture rate as 1% [2], the rate of loss would be less than 20%. The data will be analyzed statistically in the 5th years, the expectation being that at least 130 patients’ aneurysms will rupture in the first 4 years. The modeling group will be used to establish the risk of UIA rupture and compare relevant clinical information, radiological images, hemodynamic variables, genetic factors, HRMRI findings, and biomarkers [12, 13, 26–37] between the rupture and non-rupture groups to identify the risk factors for rupture. These will then be incorporated into a multi-dimensional model for predicting risk of UIA rupture. The validation group will then be used to validate that model (Fig. 2).

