This study will incorporate nested screening of 500 individuals from cohort 1 (CIAP-1). Recruitment for this study started in September 2016. The estimated primary completion date will be in December 2020. The project will produce preliminary results in the 5th year. After the end of the 5th year, we will have a longer follow-up visit to the patients who have been in the group.

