### Model building (first set of UIA queues)

The following possible or established risk factors for UIA will be collected and analyzed: age; sex; blood pressure, smoking, alcohol consumption, hyperlipidemia, diabetes mellitus, and family history of subarachnoid hemorrhage, intracranial aneurysm, and autosomal dominant diseases (polycystic kidney, Marfan syndrome, collagen dysplasia, etc.)The following imaging data will be collected and analyzed: shape, location, size, aspect ratio and odds ratio of aneurysms, morphological factors such as the angle of the aneurysm jet, and known risk factors for rupture.In our experience, follow-up angiography alone does not adequately predict the outcome whereas HRMRI is a more useful means of following these lesions [38]. We have also found and reported that aneurysm wall enhancement on HRMRI predicts instability of an intracranial aneurysm [39]. HRMRI will be performed on patients enrolled in the UIA follow-up cohort at the 20 participating centers and HRMRI-identified aneurysm wall enhancement assessed as a possible predictor of UIA rupture. Two-dimensional short-axis images of the aneurysms generated from the registered pre-and post-contrast T1w-SPACE images will be used to identify wall enhancement [13].To identify risk factors, the nested cohort study will incorporate the following: incidence of aneurysm rupture in the follow-up cohort, the definition of UIA recently rupture before the duration of follow-up was high risk of rupture of UIA, acquisition of imaging data for hemodynamic calculations; according to the aneurysm ratio of 1:2 UIA (rupture vs non-rupture), and analysis of differences in hemodynamic variables, genetic factors, and biomarkers.A.Analysis of hemodynamic variables: A three-dimensional shape will be created and image data from computed tomographic angiography, magnetic resonance angiography, or DSA saved as DICOM files. Once the 3D model has been reconstructed, it will be saved in an STL file format. A rigid wall in the parent vessel and aneurysm will be assumed in the simulation of hemodynamics. We will start by using ANSYS ICEM CFD (Materialise, Leuven, Belgium) to build a finite element model, then perform a simulation on ANSYS CFX software (Materialise), and finally use ANSYS CFX POST postprocessing to calculate Wall Shear Stress (WSS), maximum wall shear stress (WSSmax), low WSS areas, steady state of blood flow, and so on. Our team has already identified that these factors are associated with the stability of aneurysms [40–42].B.Gene and biomarker analysis: Blood samples will be collected from all participants and specimens of the aneurysm wall from patients who undergo craniotomy. Target chromosomes will be tested for blindly. Target genes and biomarkers identified as possibly relevant by the latest international research will be tested. Differences in genes and biomarkers between rupture and non-rupture groups will be compared to identify rupture-related factors.

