## Statistical methods

### Total sample size

CIAP-1: Calculation of the required sample size using an expected annual rupture rate of 1%, allowable error of d = 0.6%, and alpha = 0.05 on two-sided testing indicated that 1173 patients need to be enrolled per year, that is, 4692 over 4 years. An annual rupture rate of 1% [2] results in a loss rate of less than 20%. A reported hemodynamic index (complex flow patterns OR = 4.7) and HRMRI index (aneurysmal wall enhancement OR = 3.05 for ruptured versus unruptured aneurysm) also indicate that this sample size would be sufficient [12, 43]. Given that genetic factors have not yet been evaluated [35], our genetic testing will assess previously reported possible genetic indicators of prognosis; additionally, target genes and biomarkers will be selected according to the latest research progress in the future. In the 5th year of the study, we will analyze the data. As previously mentioned, at least 130 aneurysms are expected to rupture in the modeling group in the first 4 years. Allowing for a loss rate of 20%, the study will need to enroll 500 individuals.

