### Expected loss rate (less than 20%)

The expected loss includes all patient data excluded from the main analysis, usually because of a serious breach of the study protocol by the principal investigator (affecting the evaluation of the primary endpoint of effectiveness). Possible such breaches include failure to meet the inclusion/exclusion criteria; failure to follow the prescribed schedule; follow-up visits not occurring within the specified time limits, and concomitant treatments that may affect incidence of rupture. However, excellent clinical follow-up may achieve a drop-out rate of as little as 5%.

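### The 20% loss allowance behind the 500 enlarges the nested sample but cannot add ruptures; if 130 is the modeling-group count before loss, a 1:2 sample stops at about 390

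*Protocol article*

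**What the plan says.** Four statements in the protocol article bear on the size of the nested sample.

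- *Model building (first set of UIA queues)* gives the sampling ratio for the hemodynamic, genetic and biomarker comparisons: "according to the aneurysm ratio of 1:2 UIA (rupture vs non-rupture".
- *Total sample size* says that "at least 130 aneurysms are expected to rupture in the modeling group in the first 4 years" and continues: "Allowing for a loss rate of 20%, the study will need to enroll 500 individuals".
- *Design* gives the same count without tying it to one group ("the expectation being that at least 130 patients’ aneurysms will rupture in the first 4 years") and divides the follow-up cohort into "a modeling and a validation group, in a ratio of 2:1".
- *Data collection and management* says where the 500 come from: "This study will incorporate nested screening of 500 individuals from cohort 1 (CIAP-1".

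*Expected loss rate* defines loss by exclusion from analysis ("The expected loss includes all patient data excluded from the main analysis"), with no exemption for patients whose aneurysm ruptured. *Model building* also says that the nested risk-factor work covers the whole of CIAP-1, and reserves the second group for masked checking of the finished model.

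**The concern.** Dividing by one minus the loss rate is sound when recruitment can be extended until enough patients are evaluable. A nested sample selected on outcome is different. The parent cohort fixes the number of ruptures, and only the non-rupture side can be enlarged. Under a 1:2 rule the loss allowance therefore adds places that have no ruptures to match them.

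What is at stake is the stated number of cases behind the comparisons that distinguish CIAP-2. A reader of *Total sample size* would conclude that enrolling 500 secures 130 analyzable ruptures. The plan's own inputs point to fewer, and to part of the 500 going unused.

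**Working it through.** **Inputs from the article.** Ratio 1:2; at least 130 ruptures; loss 20%; nested total 500; annual rupture rate 1%; cohort 5000; modeling:validation 2:1; four years.

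**1. Reproducing the 500.** The article shows no formula. The combination of its own figures that comes close is:
- 130 × (1 + 2) = 390
- 390 / 0.8 = 487.5, rounded up to 488, within 3% of 500

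The alternative 390 × 1.2 = 468 fits less well.

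**2. Ruptures that this total needs at 1:2.**
- 500 / 3 = 166.7, so 167
- 488 / 3 = 162.7, so 163

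With 130 ruptures the 1:2 sample is 130 + 260 = 390, which leaves 500 − 390 = 110 places unfilled.

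**3. Is 130 before or after loss?**
- Modeling group before loss: 5000 × 1% × 4 × 2/3 = 133.3 (compounded: 5000 × (1 − 0.99⁴) × 2/3 = 131.3)
- Modeling group after 20% loss: 133.3 × 0.8 = 106.7

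The pre-loss figure matches 130. The calculation credits every patient with four full years, so it is a generous one. With the calculated CIAP-1 size of 4692 it gives 4692 × 4% × 2/3 = 125.1.

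**4. What remains for analysis.** If 20% is lost equally from ruptured and non-ruptured patients (assumption):
- 130 × 0.8 = 104 ruptures
- 260 × 0.8 = 208 controls

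**5. Precision.** Log-OR variance is taken as proportional to 1/cases + 1/controls.

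| Cases : controls | √(1/cases + 1/controls) | Relative to 130:260 |
|---|---|---|
| 130 : 260 (implied) | 0.1074 | 1.000 |
| 104 : 208 (1:2, 20% lost) | 0.1201 | 1.118 |
| 130 : 370 (all 500 used, no loss) | 0.1020 | 0.949 |
| 104 : 296 (all 500 used, 20% lost) | 0.1140 | 1.061 |

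Moving from 1:2 to 1:2.85 multiplies the SE by 0.949 and the variance by 0.949² = 0.90, with or without the loss. The gain grows if ruptures are fewer. With 100 ruptures, an illustrative figure, 500 places allow 1:4, and the variance ratio is (1 + 1/4) / (1 + 1/2) = 0.83.

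**6. Power.** Two-proportion calculation, with an assumed exposure of 10% to 50% in non-ruptured patients.
- OR 3.05 (cited for wall enhancement), 104:208: 0.927 or higher
- OR 4.7 (cited for flow pattern), 104:208: 0.999 or higher
- OR 2.0 (assumed): 0.531–0.805 with 104:208; 0.584–0.845 with 104:296; 0.619–0.885 with 130:260

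**The case against.** A reader might infer that the 500 places simply cannot be filled. The documents do not support that without conditions. The count is a floor, and *Total sample size* assigns it to the modeling group only. The text also never says that 500 is a 1:2 sample, or that 1:2 is an upper limit. Three readings could rescue the figure.

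- **Ruptures come from the whole cohort.** *Model building* can be read this way. Then 130 × 1.5 = 195, or 5000 × 4% = 200, ruptures are expected, and 195 × 3 = 585 exceeds 500. This does fill the places, but it uses the validation group's ruptures to build the model that this group is meant to test. After 20% loss it gives 200 × 0.8 = 160 ruptures, or 480 places.
- **130 is already net of loss.** The 488 is then consistent. But 130 / 0.8 = 162.5 modeling-group ruptures must occur, which is 162.5 × 1.5 = 244 in the cohort, against 200 at the stated rate.
- **The 500 are enrolled prospectively, not selected by outcome.** The wording on screening and enrollment allows this. But 500 × 1% × 4 = 20 ruptures, which cannot be the source of 130.

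A second tempting inference is that the nested study is underpowered. For the two odds ratios that the article cites, power stays high even at 104:208. The shortfall matters for weaker factors, and the article gives no effect size for genes or biomarkers.

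Some of the objection stands. The 488 formula is inferred. The equal split of loss is assumed, and the article calls 20% an upper bound with 5% possible. Unfilled control places alone cost only about 5% in SE; losing ruptured patients costs more, about 12%.

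**Conclusion.** The point holds conditionally. If 130 is the pre-loss count for the modeling group, which the stated 1% rate best supports, then a 1:2 sample stops at about 390. A 20% loss falling equally on both groups leaves about 104 + 208 for analysis, not 130 + 260. The loss allowance cannot supply the 163 to 167 ruptures that 488 to 500 places need. Among the readings consistent with the stated rate, only the whole-cohort one fills 500 at 1:2, and it does so with ruptures reserved for validation.

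The effect is moderate: about 12% in SE from the lost cases, and about 5% in SE (10% in variance) that could be gained by using the unfilled places. Enrolling more people into the nested set cannot restore the lost cases. The conclusion rests on the inferred formula, four full years of follow-up for all patients, and loss at the plan's upper bound.

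**What to change.** Reconcile *Design*, *Model building* and *Total sample size* on three points: which group the 130 refers to, whether it is before or after loss, and whether the nested sample draws on the modeling group or the whole cohort.

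If 130 is the pre-loss modeling-group count:
- state the ruptures available for analysis as about 104 at 20% loss, and do not imply that enrolling 500 restores the remainder;
- define 500 as a fixed total of all eligible ruptures plus eligible non-rupture controls filling the remaining places, with 1:2 as the minimum ratio.

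The change is one of wording, with no patients beyond the planned 500. Because "Blood samples will be collected from all participants", no new blood sampling is implied. The small downside is assays and flow simulation on up to about 110 more controls than a strict 1:2 rule would use.

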### Aims

CIAP is a multicenter, large prospective study of intracranial aneurysms that has five different facets: CIAP-1 is for setting up and managing a UIA queue of 5000 individuals and calculating the annual rate of rupture of those aneurysms; CIAP-2 for exploring risk factors associated with aneurysm rupture and developing a multidimensional model for predicting aneurysm rupture; CIAP-3 for exploring antithrombotic therapy in patients with UIA complicated by ischemic cardio-cerebrovascular diseases; CIAP-4 for comparing treatment options for UIA-intervention and craniotomy, the study protocol of CIAP-4 has been published [25]; and CIAP-5 is for development of standardized treatments for early-stage bleeding from aneurysms. CIAP-1 is responsible for the management of the UIA queue. This is for the second observational study. An overview of the CIAP design is presented in Fig. 1.

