Risk factors for rupture, including hemodynamic variables, genes, and biomarkers will be calculated in a nested cohort study of the entire first cohort (CIAP-1: the first project of the China Intracranial Aneurysm Project and is managed by Tangdu Hospital, Fourth Military Medical University). A multi-dimensional model for predicting UIA rupture and bleeding that incorporates clinical, imaging, HRMRI data, and so on will be constructed by using a statistical model.Model validation: After establishment of the model, the second group of the follow-up cohort will be used for blind verification.Comparative analyses of histopathology of aneurysm walls: When participants undergo surgery for ruptured intracranial aneurysms, the sites of rupture will be identified intraoperatively and specimens of the aneurysm wall will be removed and preserved in formalin. The location of rupture, pathological damage, hemodynamic variables, HRMRI findings, and relevant biomarkers will be analyzed to identify differences between unruptured and unruptured aneurysms. Relationships between pathological damage, hemodynamic variables, and HRMRI features of the aneurysm wall will also be assessed.

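### The Model building section places calculation of rupture risk factors in the entire CIAP-1 cohort, contradicting the Design section's restriction to the modeling group; if followed, validation would not be independent

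*Protocol article*

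**What the plan says.** The Design section of the protocol article sets up a split sample: "Individuals in the UIA follow-up cohort will be allocated to two groups, a modeling and a validation group, in a ratio of 2:1". It gives the search for predictors to the first of these: "The modeling group will be used to establish the risk of UIA rupture and compare relevant clinical information", together with imaging, hemodynamic, genetic, HRMRI and biomarker data, "between the rupture and non-rupture groups to identify the risk factors for rupture". The validation group is used only after that.

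The heading over the model-building steps agrees, since it limits them to the first set of the UIA queue. Total sample size likewise counts the expected 130 or more ruptures in the modeling group.

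Within the Model building section, however, the sentence on risk factors for rupture, naming hemodynamic variables, genes and biomarkers, says that they "will be calculated in a nested cohort study of the entire first cohort", and a parenthesis identifies that cohort as CIAP-1. The Aims section describes that project: "CIAP-1 is for setting up and managing a UIA queue of 5000 individuals". The model-validation item that follows says that "the second group of the follow-up cohort will be used for blind verification".

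**The concern.** CIAP-1 is the cohort from which both the modeling and the validation group come. A nested study of all of it would therefore include ruptures and controls from the validation third. If the comparison of ruptured with unruptured patients in that study decides which factors enter the model, the validation outcomes have already been used before the verification starts. Markers that separate the groups by chance in the validation third are then more likely to be kept, and are tested again on the same patients.

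The risk is greatest for genes and biomarkers. Their number is not stated, and Total sample size leaves the choice open to future research progress. The model's measured accuracy in the validation group is the main evidence the study would offer for clinical use, so it matters that this group is untouched.

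**Working it through.** **1. Is the validation third inside CIAP-1?** Inputs: 5000 patients (Aims); annual rupture rate 1% and modeling share 2/3 (Design); 4 years (Design and Total sample size). The stated figure is at least 130 ruptures in the modeling group (Total sample size).

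- Ruptures = patients × annual rate × years × modeling share = 5000 × 0.01 × 4 × 2/3 = 133.3. With compounding it is 131.3. Both are close to 130.
- Variants that fit less well: 4692 patients give 125.1; 5000 patients with 20% loss give 106.7.

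The figure of 130 is thus reproduced if the 2:1 split is applied to the 5000-patient CIAP-1 cohort. The validation third lies inside that cohort and holds about 200 − 133 = 67 ruptures.

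**2. Which group does the nested sample of 500 fit?** Further inputs: one rupture to two non-ruptures (Model building); 20% loss (Total sample size). Size = ruptures × (1 + 2) / (1 − 0.20).

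- Modeling group: 133.3 × 3 / 0.8 = 500. With the rounded 130 it is 390 / 0.8 = 487.5, or 488.
- Entire CIAP-1: 5000 × 0.01 × 4 = 200 ruptures, and 200 × 3 / 0.8 = 750.

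The stated 500 agrees with a nested study in the modeling group, not in the whole cohort. The article writes out neither derivation; both are inferred from its own inputs.

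**3. The passages side by side.**

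| Place | Where risk factors are identified |
|---|---|
| Design | Modeling group |
| Heading of Model building | First set |
| Total sample size (130 ruptures, 500 individuals) | Modeling group, by the arithmetic above |
| Sentence on risk factors in Model building | Entire first cohort, named as CIAP-1 |

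**4. What would follow if the last row were applied?** Assumptions, none of them fixed by the article: all candidates are independent pure noise; each is screened by a t-test at P<0.05; coefficients are fitted in the modeling group only; 133 modeling and 67 validation ruptures, each with two controls; 10 to 100 candidates. Mean AUC in the validation group by simulation:

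| Candidates | Screening in whole cohort | Screening in modeling group only |
|---|---|---|
| 10 | 0.52 (0.52 to 0.53 across runs) | 0.50 |
| 20 | 0.54 | 0.50 |
| 50 | 0.57 | 0.50 |
| 100 | 0.60 | 0.50 |

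The true AUC is 0.50 in every row, so the excess over 0.50 comes only from letting the validation outcomes take part in the screening.

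**The case against.** The strongest reply is that the whole-cohort sentence is a slip. Design is explicit, and it lists the same hemodynamic, genetic and biomarker factors. The heading confines the section to the first set, validation is then given to the second group, and the 500 fits the modeling group. On this reading, first cohort stands for first set. Another benign reading is that CIAP-1 is named only as the source population, as in Data collection and management, where the 500 are described as nested in that cohort.

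Much of this stands. A reader might infer that the plan is settled on using validation patients to choose predictors; the document as a whole does not support that. Nor does it support the inference that the final model is fitted in the whole cohort: the sentence says only where risk factors are calculated, and the next one, on building the model, names no data set. P<0.05 is given for group comparisons of clinical data and not as an entry rule for the model. Because the article speaks mostly of targets already reported elsewhere, the number of candidates could be near the low end of the range.

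The reply does not remove the point. The sentence says entire and adds a parenthesis naming CIAP-1, so the slip is not self-evident. The nested step is also based on rupture incidence in the follow-up cohort, which is the cohort that is split. Someone carrying out the nested study from that section could reasonably sample both groups.

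**Conclusion.** The point holds as an internal contradiction that should be reconciled. One operative sentence in Model building conflicts with Design, with its own section heading and with the sizing in Total sample size. Which text governs decides whether the verification is independent.

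The harm is conditional. It arises only if the whole-cohort sentence is followed and its results choose the predictors. In that case, with about 200 ruptures and noise predictors, the apparent validation AUC would be about 0.52 to 0.60 for 10 to 100 candidates, where 0.50 is correct. These values illustrate the mechanism and do not forecast this study's bias, because some real candidates will carry signal and their number is not given. Larger optimism could be obtained by assuming fewer ruptures, but the article's own inputs imply about 200 for a whole-cohort study.

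**What to change.** Reword the sentence in Model building to say that risk factors, including hemodynamic variables, genes and biomarkers, are identified in a nested study of the modeling group only. State that the 2:1 split is fixed by patient before nested sampling and before any comparison by rupture outcome.

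This is a change of wording. Against a whole-cohort study, discovery would use about 133 ruptures in place of 200, one third fewer. The stated 500 participants need no change, since they already match the modeling-group option; keeping the whole-cohort sentence would call for about 750 on the same arithmetic, and the validation third could no longer serve as an independent test of the predictors chosen there.

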## Statistical methods

### Total sample size

CIAP-1: Calculation of the required sample size using an expected annual rupture rate of 1%, allowable error of d = 0.6%, and alpha = 0.05 on two-sided testing indicated that 1173 patients need to be enrolled per year, that is, 4692 over 4 years. An annual rupture rate of 1% [2] results in a loss rate of less than 20%. A reported hemodynamic index (complex flow patterns OR = 4.7) and HRMRI index (aneurysmal wall enhancement OR = 3.05 for ruptured versus unruptured aneurysm) also indicate that this sample size would be sufficient [12, 43]. Given that genetic factors have not yet been evaluated [35], our genetic testing will assess previously reported possible genetic indicators of prognosis; additionally, target genes and biomarkers will be selected according to the latest research progress in the future. In the 5th year of the study, we will analyze the data. As previously mentioned, at least 130 aneurysms are expected to rupture in the modeling group in the first 4 years. Allowing for a loss rate of 20%, the study will need to enroll 500 individuals.

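### The stated inputs for the CIAP-1 cohort give 1057 patients, not 1173 per year, and ±0.6 percentage points is not the precision of the pooled 4692

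*Protocol article*

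**What the plan says.** Under Total sample size, the protocol article sizes the CIAP-1 cohort "using an expected annual rupture rate of 1%, allowable error of d = 0.6%, and alpha = 0.05 on two-sided testing". It reports that this calculation "indicated that 1173 patients need to be enrolled per year, that is, 4692 over 4 years". The Aims section gives CIAP-1 one quantity to estimate, the annual rate of rupture, in a cohort of 5000.

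The loss figures are these:

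- Directly after the cohort size: "An annual rupture rate of 1% [2] results in a loss rate of less than 20" per cent. The Design section makes a similar link.
- At the end of the same paragraph, for the nested study: "Allowing for a loss rate of 20%, the study will need to enroll 500 individuals".
- The next section is headed "Expected loss rate (less than 20" per cent). It describes loss as data left out of the main analysis, usually for serious protocol breaches, and adds that "excellent clinical follow-up may achieve a drop-out rate of as little as 5" per cent.

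A loss of 10% appears nowhere.

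**The concern.** The article prints the inputs and the result together, so a reader should be able to get from one to the other. Three steps fail:

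- The usual formula does not return 1173.
- A requirement for a single annual rate is multiplied by 4 without a reason.
- A loss rate is presented as the consequence of a rupture rate, although loss as the article describes it comes from breaches and exclusions.

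At stake is the credibility of the stated precision. The calculation concerns the parent cohort, but it stands under this study's own sample-size heading. The paragraph then relies on that size as sufficient for the hemodynamic and HRMRI indices, and the model-building section draws risk factors from the whole first cohort.

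**Working it through.** **Inputs** (Total sample size): p = 0.01; d = 0.006, read as the half-width of the confidence interval; "alpha = 0.05 on two-sided testing", so z = 1.96.

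**Step 1. The stated figure from the stated inputs.**

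n = z² p(1 − p)/d² = 1.96² × 0.01 × 0.99/0.006² = 1056.4, rounded up to 1057.

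The printed 1173 is 11% higher (1173/1056.4 = 1.11).

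**Step 2. Other methods, same inputs, no loss allowance.**

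| Method | n |
|---|---|
| One-sided z | 744 |
| Poisson variance | 1067 |
| Jeffreys | 1085 |
| z = 2 | 1100 |
| Wilson score | 1139 |
| Agresti–Coull | 1214 |
| Continuity-corrected | 1217 |
| Clopper–Pearson | 1242 |
| Exact Poisson | 1256 |

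None returns 1173. Wilson comes closest, 34 patients (2.9%) below.

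**Step 3. Adding loss, n/(1 − L), to 1056.4.**

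- L = 5%: 1056.4/0.95 = 1112.0, so 1113
- L = 10%: 1056.4/0.90 = 1173.8
- L = 20%: 1056.4/0.80 = 1320.5, so 1321

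The loss implied by 1173 is 1 − 1056.4/1173 = 9.9%. The match at 10% is within one patient, and the printed figure is rounded down.

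**Step 4. The factor of 4.** 1173 × 4 = 4692 is correct. But the target in Step 1 is already met by one group of 1057 evaluable patients observed for a year. Four such groups are needed only if each annual intake is to have its own ±0.6-point estimate.

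**Step 5. Precision of the pooled cohort.**

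As a one-year proportion, half-width = 1.96 × √(0.01 × 0.99/N):

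- N = 4692: ±0.28 points
- N = 5000: ±0.28 points
- N = 4692 × 0.8 = 3753.6: ±0.32 points

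As a rate per person-year, half-width = 1.96 × √(0.01/PY). Assume uniform accrual over 4 years, so that mean follow-up at the end of year 4 is 2 years:

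- 4692 × 2 = 9384 person-years: ±0.20 points
- 5000 × 2 = 10,000 person-years: ±0.20 points
- 9384 × 0.8 = 7507 person-years: ±0.23 points

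**Step 6. The annual-intake reading, for comparison.** With 20% loss, 1173 × 0.8 = 938 evaluable patients per intake, and 1.96 × √(0.0099/938) gives ±0.64 points against the 0.60 intended.

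**The case against.** - **The loss figure beside the cohort size is an upper bound.** This stands. A 10% allowance lies below 20% and above the 5% best case. A reader might infer that the 1173 contradicts the plan's own loss rate, but the documents do not support that: the only flat 20% is attached to the 500. What remains is an allowance that is undeclared and differs from the one used a few lines later.
- **No formula is named, and the 10% is a reconstruction.** This also stands. The methods in Step 2 lie on both sides of 1173, so the 10% is only the likeliest explanation. Even so, none of them gives the printed number, and Wilson would leave no loss allowance at all.
- **The factor of 4 may be deliberate, and beating a maximum error is not a mistake.** This stands in part. A separate estimate for each annual intake is a possible intention, but the article does not state it, and the Aims section names one annual rate.
- **The calculation belongs to CIAP-1, whose full protocol is not shown.** This lowers the weight of the point. It does not remove it, because this article prints both the inputs and the answer and relies on the result.
- **The paragraph also cites odds ratios of 4.7 and 3.05 as support.** These concern risk factors, not the precision of a rupture rate, so they do not rescue the 1173.

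**Conclusion.** The point holds as a fault in the stated justification. The printed inputs give 1057, not 1173. An unstated loss of about 10% would explain the difference, but that is inferred. The factor of 4 does not follow from a ±0.6-point target for a single annual rate, so 0.6 is not the precision of the pooled cohort. That precision is about ±0.28 points as a one-year proportion (±0.32 for 4692 after 20% loss), or about ±0.20 points per person-year (±0.23 after 20% loss). The person-year figures rest on uniform accrual over 4 years. All figures take a true rate of 1% and, unless stated, no loss. The link from rupture rate to loss rate is not a derivation.

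A reader might go further and infer that the cohort is too small, since 4 × 1321 = 5284 exceeds both 4692 and 5000. That needs the factor of 4, which a single annual rate does not require, together with the full 20% loss. Even on the annual-intake reading the shortfall is only ±0.64 against ±0.60. For estimating the pooled rate, 4692 is more than the stated precision needs.

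**What to change.** Under Total sample size:

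1. State that ±0.6 percentage points on a one-year risk of 1% needs 1057 evaluable patients, or 1321 allowing 20% loss, and name the formula.
2. State the precision of the planned 4692 to 5000 patients: about ±0.28 points as a one-year proportion (about ±0.32 for 4692 after 20% loss), or about ±0.20 points on roughly 9,400 to 10,000 person-years by year 4 (about ±0.23 for 4692 after 20% loss). Give the uniform-accrual assumption with the person-year figures.
3. Delete the multiplication by 4, or say that it is meant to give a separate ±0.6-point estimate for each annual intake.
4. Use one stated loss allowance throughout.
5. Delete the sentence that derives the loss rate from the rupture rate, and correct the similar link under Design.

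These are text changes only; recruitment is unaffected.
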